### Trial design

This is a three-arm randomized controlled trial among Chinese MSM. Enrolled indexes will be randomly assigned to one of the three groups: standard secondary distribution, secondary distribution with monetary incentives arm, and secondary distribution with monetary incentives plus peer referral. Further, indexes will be asked to complete a baseline survey at the beginning of the trial, and a three-month follow-up survey after their HIVST kits applications. A flowchart of the trial is shown in Fig. 1.

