### Outcomes

The primary outcomes of this trial consist of three parts: 1) Mean number of motivated alters who have photo-verified self-testing per index in each arm; 2) Proportion of first-time HIV testing among alters in each arm; 3) Proportion of alters with a positive HIV testing result in each arm.

The secondary outcomes of this study consist of three parts 1) Risky sexual behavior among indexes and alters in each arm; 2) Adverse events reported during secondary distribution among indexes and alters in each arm; 3) Attitude towards and past experiences of HIVST and sexual behavior among alters in each arm.

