### Measures

In general, we aim to examine the effectiveness of our modified secondary distribution models. Primary outcomes of this trial are the number of alters, first-time testing alters, and HIV-positive alters in each arm, therefore, all testers’ information will be specifically clarified and recorded. All data will be collected through JINSHUJU, a secure online platform where participants can apply for HIVST kits, report testing results, and complete the baseline and follow-up questionnaires. All data collected from participants will be examined and deduplicated according to phone number and IP.

In the baseline survey, we will collect the socio-demographic characteristics, sexual orientation, sexual behavior, HIV testing history, and social network. When alters return the results, they will also complete a questionnaire online. In this survey, except for basic information on socio-demographic characteristics, sexual orientation, sexual behavior, HIV testing history, and social network will be collected. We will also investigate the attitudes and experiences towards self-test. The follow-up survey for indexes will take place 3 months after the application completed, which focuses on experiences and attitudes on using and distributing self-test kits. The survey mainly inquires about the occurrence of intimate partner violence (IPV) or other adverse events, the relationship between the indexes and the alters, whether indexes have tested together with the alters, and whether indexes have guided the alters on how to perform HIVST.

Specifically, in our surveys, socio-demographic characteristics include indexes’ age, sex, marital status, the highest level of education completed, and monthly income level. Sexual behavior within 3 months includes previous sex with males and females, role during sex with males, condom use, number of sex partners, and drug use. HIV testing history includes health care facility-based and online HIV testing experience. Social network collects community engagements [7], community connectedness [20], identity fusion [21], and social cohesion [22].

All blood samples will be analyzed using *SD Bioline* HIV/Syphilis duo test kits (*SD Bioline Company*, South Korea). Participants will collect fingertip blood samples by themselves according to the instruction. The trained staff of the CDC or CBO will check and read the photos of result and record them in JINSHUJU. The results are subject to the reading of the staff.

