### Sample size

According to preliminary study results, on average, the number of alters motivated by an index man was 0.65 through standard secondary distribution, 1.0 through SD/monetary incentives intervention, and 1.4 through SD/monetary incentives plus peer referral intervention. We assumed that the variances of the three groups were equal with the same standard deviation of 0.5 (preliminary data, unpublished results). Further, we estimated an effective sample size of 300 participants (100 in each group), with a power of 0.90, an alpha of 0.05, and a lost to follow-up rate of 0.20.

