### Data analysis

All statistical analyses will follow the intention-to-treat principle. Missing data will be handled by multiple imputations. Categorical variables from the baseline survey will be aggregated in frequency distributions, and numerical variables will be summarized in mean and standard deviation.

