#### Primary analysis

We will first calculate primary outcomes in each arm, i.e., mean number of alters that each index recruited, proportion of first-time HIV testers, and proportion of alter testers with an HIV-positive result. Secondly, we will compare calculated means using two-sample t-test, and proportions using chi-square between SD/monetary incentives arm and control arm, SD/monetary incentives plus peer referral arm and control arm, and also between two intervention arms.

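### The primary count is compared by an unadjusted t-test although plausible baseline predictors are collected: a possible, minor loss of precision, not a bias

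*Protocol article*

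**What the plan says.** The first primary outcome in the Outcomes section is "Mean number of motivated alters who have photo-verified self-testing per index in each arm". For the three pairwise comparisons of arms, the Primary analysis section states: "we will compare calculated means using two-sample t-test, and proportions using chi-square". It names no covariate.

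The Measures section lists what is known about each index at entry: "In the baseline survey, we will collect the socio-demographic characteristics, sexual orientation, sexual behavior, HIV testing history, and social network". The sexual behaviour items cover three months and include "condom use, number of sex partners, and drug use". The social network items are four scales: community engagement, community connectedness, identity fusion and social cohesion.

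The Data analysis section gives these data a descriptive role: "Categorical variables from the baseline survey will be aggregated in frequency distributions", with means and standard deviations for the numerical ones. The Follow-up section adds a before-and-after comparison of index behaviour. No adjusted, stratified or regression analysis of the count appears anywhere in the article.

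On timing, the Trial design section says that "indexes will be asked to complete a baseline survey at the beginning of the trial". It does not say whether the survey comes before or after allocation.

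**The concern.** Under the Interventions section, kits go to people such as sexual partners and friends. An index's number of partners, testing history and ties to the community therefore plausibly bear on how many alters he brings to a verified test. A test that ignores such variables leaves in the error term any variation they could have explained.

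This is not a detail left open for an analysis plan, because the article names the test. The point concerns what is fixed. What could be lost is the width of the confidence intervals and, if the count is more dispersed than the sample-size section assumes, some power for the two smaller contrasts, on which Hypotheses 1 and 3 rest.

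**Working it through.** **Inputs from the Sample size section.** The means are given as follows: "was 0.65 through standard secondary distribution, 1.0 through SD/monetary incentives intervention, and 1.4 through SD/monetary incentives plus peer referral intervention". The differences are 1.0 − 0.65 = 0.35, 1.4 − 1.0 = 0.40 and 1.4 − 0.65 = 0.75. The SD is 0.5 in all arms, power 0.90, alpha 0.05 (taken as two-sided) and loss 20%. With 100 per arm, 100 × 0.80 = 80 are evaluable.

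**Assumed, because the documents give no figure.** R-squared, the share of outcome variance explained by the covariates, is set at 0.10 and 0.20. The alternative variance models below are also assumptions.

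**Plan's own figure.** n per arm = 2 × 0.5² × (1.960 + 1.282)² / 0.35² = 42.9, so 43. Then 43 / 0.80 gives 54 per arm and 162 in total. The stated 300 is not reproduced and exceeds what its inputs require. That is a separate matter, and nothing below depends on it.

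**Formulas (normal approximation).**
- SE = √[(V₁ + V₂)(1 − R²)/n], where V₁ and V₂ are the arm variances
- 95% half-width = 1.96 × SE
- Power = Φ(difference/SE − 1.96)
- Relative narrowing of the interval = 1 − √(1 − R²)
- Equivalent sample size = n/(1 − R²)

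**Step 1: the protocol's SD of 0.5, 80 per arm, difference 0.35.**

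| R² | SE | Half-width | Power |
|---|---|---|---|
| 0 | 0.0791 | 0.155 | 99.3% |
| 0.10 | 0.0750 | 0.147 | 99.7% |
| 0.20 | 0.0707 | 0.139 | 99.9% |

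With 100 per arm, unadjusted power is 99.9%. Power is already saturated. The gain is a narrower interval: 1 − √0.90 = 5.1% and 1 − √0.80 = 10.6%. That precision equals having 1/0.90 = 1.11 or 1/0.80 = 1.25 times as many participants.

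**Step 2: is an SD of 0.5 plausible for this count?** The smallest SD an integer variable can have is √[f(1 − f)], where f is the fractional part of its mean.
- Mean 0.65: √(0.65 × 0.35) = 0.477
- Mean 1.4: √(0.4 × 0.6) = 0.490

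In those two arms, 0.5 is almost the floor; it would require nearly every index to bring 0 or 1 alter (mean 0.65), or 1 or 2 (mean 1.4). The mean of 1.0 sets no such floor. Poisson SDs would be √0.65 = 0.81, 1.00 and √1.4 = 1.18. A larger spread is therefore likely, but its size is not known.

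**Step 3: larger variance, 80 per arm.** Poisson variance is μ. Negative binomial variance with k=1 is μ + μ². For 0.65 versus 1.0, V₁ + V₂ is 1.65 (Poisson) or 1.0725 + 2 = 3.0725 (negative binomial). The unadjusted SE is √(1.65/80) = 0.144 or √(3.0725/80) = 0.196.

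| Variance model | Contrast | R² = 0 | R² = 0.10 | R² = 0.20 |
|---|---|---|---|---|
| Poisson | 0.65 vs 1.0 | 68% | 73% | 78% |
| Poisson | 1.0 vs 1.4 | 64% | 68% | 73% |
| Neg. binomial, k=1 | 0.65 vs 1.0 | 43% | 47% | 51% |
| Neg. binomial, k=1 | 1.0 vs 1.4 | 34% | 37% | 41% |

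With 100 per arm, the unadjusted figures for 0.65 versus 1.0 are 78% (Poisson) and 51% (negative binomial). Adjustment adds about 4 to 5 percentage points at R² = 0.10 and about 7 to 10 at 0.20 in these scenarios.

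**The case against.** The strongest reply is that nothing here is wrong. A two-sample t-test between randomised arms is unbiased and conventional, and a covariate list is often left to an analysis plan that is not shown. Validity is granted in full. The point survives only because the article commits to a specific unadjusted test while describing data that could sharpen it.

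The second reply is that the benefit depends on assumptions about both R-squared and dispersion, neither of which the documents supply. That also stands. At SD 0.5 adjustment is not needed for power. At k=1 it does not rescue power.

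Three stronger readings are tempting and not supported:

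- A reader might infer that the two smaller contrasts have little power to spare. On the protocol's own inputs they have more than 99%. The lower figures arise only under a larger assumed variance.
- A reader might infer that adjustment is needed to remove chance imbalance as a rival explanation for a difference. The t-test's error rate already allows for chance imbalance.
- A reader might assume that network size or number of male partners is available for adjustment. The Measures section names neither. It lists number of sex partners and four community scales.

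Finally, adjustment is safe only for covariates measured before allocation, and the article does not state that order.

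**Conclusion.** The point holds as a minor improvement. The plan fixes a valid but unadjusted test for its first primary outcome and leaves plausible predictors unused. The consequence is a possible loss of precision, with no bias and no inflation of type I error.

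Its size cannot be read from the documents. If R-squared is 0.10 to 0.20, intervals are about 5% to 11% narrower whatever the variance. Whether that matters for power depends on dispersion: not at SD 0.5, and by roughly 3 to 10 percentage points under the Poisson and k=1 scenarios with 80 per arm. If the covariates are not prognostic, nothing is gained. The calculations use a normal approximation, two-sided alpha of 0.05 for each contrast, and the same R-squared in every arm.

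**What to change.** Before analysis starts (the Trial status section says it has not begun), name as the primary comparison a linear regression of the per-index count on arm plus a short pre-specified list of collected baseline items. Number of sex partners in the past three months, HIV testing history and community connectedness would be one reasonable list. Use heteroscedasticity-robust standard errors. The identity link keeps the target as a difference in mean alters per index, so the outcome definition does not change. Read all three pairwise differences from this one model, and keep the unadjusted t-test as supportive.

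Confirm first that each chosen item was recorded before allocation, and leave out any that was not. State how missing covariate values will be handled.

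The cost is a change of wording, a little more analysis work and a rule for missing covariates. No new data are needed. Fixing the list now also avoids the appearance of choosing covariates after seeing results.

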#### Secondary analysis

Results of the follow-up survey for indexes and the survey for alters will be used for measuring secondary outcomes, i.e. risky sexual behavior, adverse events during secondary distribution, and experience and attitude towards HIV testing. High-risk sexual behavior, defined as unprotected sex, substance use, or multiple sexual partners, are determined from survey questions such as “How often do you wear a condom during anal sex?”, “In the past three months, how many sexual partners did you have?”, “In the past three months, have you used drugs before sex?”, etc. Adverse events or IPV that happened on alters during distribution are determined from the question “Have you experienced any of the following IPV when received the HIVST kit from the index?”. Alters’ experience and perception of HIVST are determined from total 20 question items, e.g. “How difficult do you feel about completing HIV self-testing?”, “How many men did you have anal sex with after HIV self-testing?”, “Which testing do you prefer, facility-based testing or HIV self-testing?”, etc. We will use chi-square tests to compare each outcome of interests between SD/monetary incentives group and control group, SD/monetary incentives and peer referral group and control group, and also between two intervention arms.

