**Methods:**

Three hundred MSM in China will be enrolled through a digital platform for data collection. The eligibility criteria include being biological male, 18 years of age or over, ever having had sex with another man, being able to apply for kits via the online platform, and being willing to provide personal telephone number for follow-up. Eligible participants will be randomly allocated into one of the three arms: standard secondary distribution arm, secondary distribution with monetary incentives arm, and secondary distribution with monetary incentives plus peer referral arm. Participants (defined as “index”) will distribute actual HIV self-test kits to members within their social network (defined as “alter”) or share referral links to encourage alters to apply HIV self-test kits by themselves. All index participants will be requested to complete a baseline survey and a 3-month follow-up survey. Both indexes and alters will complete a survey upon returning the results by taking a photo of the used kits with the unique identification number.

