#### Secondary distribution with monetary incentives plus peer referral (SD/monetary incentives plus peer referral) arm

Index MSM in this arm will first receive the same intervention as the participants received in the monetary incentives arm. In addition, apart from applying for up to five self-testing kits, each index MSM in this arm will obtain a unique referral link, which can be shared with up to 5 individuals within their social network to apply for kits, and each alter can apply for only one kit through the link. Similarly, indexes will be given 20 RMB for each matched alter who returns the result (whether through peer referral or direct distribution). All testers will receive a monetary incentive of 20 RMB once they complete uploading their results.

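### The only harm item named for alters asks about receiving the kit from the index, so it does not clearly cover link-recruited alters, who exist only in the peer-referral arm

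*Protocol article*

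**What the plan says.** The Outcomes section lists as a secondary outcome: "Adverse events reported during secondary distribution among indexes and alters in each arm". For the alter side, the Secondary analysis section fixes the source: "Adverse events or IPV that happened on alters during distribution are determined from the question" is followed by a single item, "Have you experienced any of the following IPV when received the HIVST kit from the index".

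The description of the peer-referral arm adds a second supply route. There, "each index MSM in this arm will obtain a unique referral link, which can be shared with up to 5 individuals within their social network", and "each alter can apply for only one kit through the link". The abstract likewise separates handing over actual kits from the option to "share referral links to encourage alters to apply HIV self-test kits by themselves". The index is paid for each matched alter who returns a result, "whether through peer referral or direct distribution", so link-recruited alters belong to that arm.

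The comparison is pairwise between arms. The sentence beginning "We will use chi-square tests to compare each outcome of interests between SD/monetary incentives group and control group" goes on to name the other two pairs and mentions no split by route.

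**The concern.** The item ties IPV to one moment: the index handing over the kit. For an alter who was sent a link and ordered his own kit, that moment does not clearly exist. Such alters occur in one arm only, so any resulting loss of events falls on one side of two of the three planned comparisons.

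This outcome carries the alter side of the trial's safety reporting. In both incentive arms the index earns 20 RMB for each alter who returns a result, so pressure on an alter is a foreseeable harm. As written, the item may not register it in the route that distinguishes the third arm. The Discussion foresees wider implementation if the strategy succeeds. A finding of no excess IPV with peer referral would then be hard to interpret, because part of that arm's alters may have had no suitable question to answer.

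**Working it through.** The protocol states no IPV rate, link share or power for this outcome, so there is no figure of its own to reproduce. The check is a reading of the text followed by a dilution calculation on assumed values.

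**Step 1. Reading the sections together.**
- *Measure.* In Secondary analysis, the items for risky sexual behaviour and for experience of self-testing are marked as examples. The alter IPV item is not: it is given as the question from which the outcome is determined.
- *Other alter harm items.* The Measures section describes the alter survey as background, behaviour, testing history, social network, and attitudes and experiences. It names IPV and other adverse events only for the index follow-up survey.
- *Route.* The control and incentives-only arms have direct distribution alone. Only the third arm has the link.
- *Denominator.* Link-recruited alters are matched to their index and belong to the arm. Nothing says whether they are counted for this item.

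**Step 2. Formula.** Let f be the share of the third arm's alters recruited by link, p_D the IPV risk in directly supplied alters and p_L the risk in link-recruited alters.
- True rate in the arm: (1 − f) × p_D + f × p_L.
- Recorded rate if link alters answer 'no' and are counted: (1 − f) × p_D.
- Shortfall: f × p_L. It is zero if p_L = 0 and otherwise positive. On this branch the recorded rate does not depend on p_L at all.
- With equal risk by route (p_L = p_D = p), the recorded rate is p × (1 − f), and a true risk ratio of 1/(1 − f) against the incentives-only arm would be recorded as no difference.

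**Step 3. Illustrative numbers.** The Sample size section expects 1.0 alters per index with incentives and 1.4 with incentives plus referral. If direct distribution is the same in both arms, f = (1.4 − 1.0)/1.4 = 0.286. The 5.0% rate and the other link shares are assumptions with no source in the documents. With equal risk by route:

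| Link share f | Recorded when truth is 5.0% | True risk ratio recorded as 1 |
|---|---|---|
| 10% | 5.0 × 0.90 = 4.5% | 1/0.90 = 1.1 |
| 29% | 5.0 × 0.714 = 3.6% | 1/0.714 = 1.4 |
| 50% | 5.0 × 0.50 = 2.5% | 1/0.50 = 2.0 |

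**Step 4. Dropping equal risk.** Keep f = 0.286 and p_D = 5.0%, so the recorded rate is 3.6%.
- p_L = 0: true rate 3.6%, shortfall nil.
- p_L = 5.0%: true rate 5.0%, shortfall 1.4 percentage points.
- p_L = 10%: true rate 0.714 × 5.0 + 0.286 × 10 = 6.4%, shortfall 2.9 percentage points.

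**Step 5. If link alters skip the item and are dropped.** The recorded rate is p_D = 5.0%. That equals the arm's true rate when p_L = 5.0%, is too high when p_L = 0 (3.6%) and too low when p_L = 10% (6.4%). The direction is then not fixed, and link-route harm is simply not observed.

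**Step 6. Control versus incentives alone.** Here f = 0 in both arms, so this mechanism has no effect.

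**The case against.** The strongest reply is that the questionnaire itself is not shown. The article prints one English line from an online survey. The response options, any not-applicable choice and any separate version for link applicants may stand elsewhere. This has weight: it rules out saying how link-recruited alters will respond. It does not remove the point, because the protocol presents this one question as the source of the outcome and its wording fits one route only.

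A reader might infer that link-recruited alters are bound to answer 'no', that the bias always favours peer referral, and that a false safety result is built in. The documents do not support this. They define no denominator for the item, and an alter may skip it or read receipt of the kit loosely. They do not describe how link-ordered kits are delivered, so it is an inference that the index never hands one over. Nor do they say that risk is equal by route: an alter who need not take a kit from the index may truly have lower risk, and then little is missed.

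It is also fair that the harm outcome does not rest on this item alone. Under Measures, the index follow-up survey asks about IPV and other adverse events without limiting this to kit receipt. That covers the index side. It is not the alter's own report, so it does not replace the alter measure.

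**Conclusion.** The point stands as a gap in coverage that can become a bias. The named item does not clearly apply to link-recruited alters, they occur in one arm only, and the planned comparison does not separate routes. Link-route harm is therefore unmeasured or under-recorded.

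A downward bias in the peer-referral arm follows if three conditions hold: link alters answer 'no', they remain in the denominator, and some of them do experience IPV. Its size cannot be derived from the documents. The drop from 5.0% to 3.6% is an illustration that also needs a 29% link share and equal risk by route. The two comparisons involving the peer-referral arm are exposed; control versus incentives alone is not. The correction should be made, since it is cheap and concerns safety reporting.

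**What to change.** 1. Reword the alter item so that it fits both routes: IPV from the index in connection with being given the kit, being sent the link, or being asked to test.
2. Record which version of the item each alter answered. State how link-recruited alters surveyed under the old wording are counted.
3. Report alter events by route, direct or link, within the peer-referral arm.
4. For alters surveyed under the old wording, restrict the between-arm IPV comparison to directly supplied alters or present it by route. State that this is not a fully randomised comparison, because the route is chosen after allocation.
5. Keep the per-alter rate as the measure. Events per index may be shown beside it but should not replace it, because they mix harm with reach. At an identical 5% risk per alter, the planned 0.65, 1.0 and 1.4 alters per index give 0.033, 0.050 and 0.070 events per index. Keep alter and index reports separate, so that one incident is not counted twice.

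The cost is one reworded online item, one version field and one extra table. The Trial status section reports that enrolment was continuing and analysis had not begun, so the change could still help. The drawbacks are two item versions within one secondary outcome, and alters who never upload a result remain unobserved.

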### Follow-up

The follow-up survey will be administered 3 months after indexes apply for HIVST kits. This survey focuses on distribution history, the relationship between indexes and alters, and indexes’ risky sexual behavior. The results from follow-up survey will be compared with baseline survey results to investigate whether the index MSM has changed their behavior after HIVST. Xutong’s volunteers will check returned self-test results. If there is any positive (reactive) result returned, volunteers will contact testers accordingly, and refer them to the local CDC to do confirmation tests. Moreover, reactive testers will be encouraged to distribute HIVST kits to their sexual partners or provide partners’ contact information to volunteers for offering free testing service.

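### The between-arm test of indexes' risky sexual behaviour leaves out the baseline already collected, and a between-arm difference in alters' behaviour, asked at result upload, would mainly show who each arm reached

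*Protocol article*

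**What the plan says.** The Outcomes section lists as a secondary outcome "Risky sexual behavior among indexes and alters in each arm". The Secondary analysis section names the data source: "Results of the follow-up survey for indexes and the survey for alters will be used for measuring secondary outcomes". It defines high-risk behaviour by three yes/no type components (unprotected sex, substance use, multiple partners) and fixes the test: "We will use chi-square tests to compare each outcome of interests between SD/monetary incentives group and control group". The same test is used for the other two pairs of arms. No baseline term appears.

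The baseline data exist. The Measures section says "In the baseline survey, we will collect the socio-demographic characteristics, sexual orientation, sexual behavior, HIV testing history, and social network" and describes the sexual-behaviour items as covering three months, including condom use, number of partners and drug use. The Follow-up section gives the only stated use of the index baseline for this outcome: "The results from follow-up survey will be compared with baseline survey results to investigate whether the index MSM has changed their behavior after HIVST".

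For alters, the Measures section says "When alters return the results, they will also complete a questionnaire online". The Abstract and the description of the control arm give the same timing. Only indexes have a 3-month follow-up survey. Among the alter questions in the Secondary analysis section is "How many men did you have anal sex with after HIV self-testing".

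**The concern.** **Indexes.** Two sections describe two analyses of the same outcome and do not join them. The Follow-up section compares before with after. Every arm receives self-test kits, so that comparison has no untreated comparator and cannot by itself attribute a change to self-testing. Calendar time is one competing explanation: the Trial status section reports that the pandemic disrupted the study while enrolment was running. The Secondary analysis section compares the randomized arms, which is the comparison that can support a conclusion, but does so without the baseline value of the same behaviour, likely one of its better predictors.

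**Alters.** Alters enter after randomization, through an intervention meant to change how many are reached and, in the stated purpose, to reach more first-time testers. Randomization does not make them comparable across arms. Their behaviour is asked when the result is uploaded, looking back three months. If a difference were read as the arms changing sexual risk (for instance, as risk compensation), that reading would go beyond what the data can show.

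**Working it through.** The protocol states no sample size, power, rate or correlation for risk behaviour, so there is no figure of its own to reproduce here. The calculations below only indicate size.

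**Indexes: what baseline adjustment might be worth**

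Inputs: 100 per arm and 20% loss (Sample size section), so 100 × (1 − 0.20) = 80 evaluable per arm. Assumed: 50% versus 35% with the behaviour at 3 months, two-sided alpha 0.05, and a baseline-to-follow-up correlation r.

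Unadjusted power = Φ{[|p1 − p2|·√n − 1.96·√(2·p̄(1 − p̄))] / √[p1(1 − p1) + p2(1 − p2)]}, with p̄ = 0.425. This gives Φ{[0.15·√80 − 1.96·0.699] / 0.691} = Φ(−0.041) = 0.48.

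Approximate adjustment: replace n by n/(1 − r²).

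| r between the analysed items | 1 − r² | effective n per arm | power |
|---|---|---|---|
| 0 (unadjusted) | 1.00 | 80 | 0.48 |
| 0.3 | 0.91 | 87.9 | 0.52 |
| 0.5 | 0.75 | 106.7 | 0.60 |
| 0.7 | 0.51 | 156.9 | 0.77 |

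The 1 − r² rule belongs to a linear model of a continuous measure. The planned outcomes are binary, and splitting a measure into yes/no weakens its correlation over time. If two normal measures correlate at r and both are split at the median, the yes/no items correlate at φ = (2/π)·arcsin(r):

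- r = 0.5: φ = (2/π) × 0.524 = 0.33; 1 − φ² = 0.89; effective n = 80/0.889 = 90; power 0.53.
- r = 0.7: φ = (2/π) × 0.775 = 0.49; 1 − φ² = 0.76; effective n = 80/0.756 = 105.8; power 0.60.

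So an underlying correlation of 0.5 to 0.7 cuts variance by 25% to 51% for a continuous measure, but only by about 11% to 24% for the binary items.

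**Alters: timing**

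- Outcome: risk behaviour among alters, by arm (Outcomes).
- Source: the alter survey (Secondary analysis).
- Time of that survey: when the result is returned (Abstract, control arm description, Measures).
- Recall: three months (Measures; two of the three quoted items in Secondary analysis. The quoted condom item states no window).
- Later alter survey: none described.

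The recall window ends at upload, so it lies largely before the test. The item on sex after self-testing can cover only the time between test and upload. The protocol does not give that interval.

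**Alters: how a difference can arise without any change in behaviour**

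Inputs: planned means of 0.65, 1.0 and 1.4 alters per index (Sample size). With 100 indexes per arm this gives 65, 100 and 140 alters. Assumed: no arm changes behaviour, but 40% of the alters reached in the control arm are at risk against 50% to 60% in an intervention arm. Treating alters as independent, the probability of p < 0.05 with the intervention arm higher is:

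| comparison | 40% vs 50% | 40% vs 60% |
|---|---|---|
| 65 vs 100 alters | 0.24 | 0.71 |
| 65 vs 140 alters | 0.26 | 0.77 |

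A significant result here would be a true statement about who was reached and would say nothing about changed behaviour.

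**The case against.** A reader might infer that the plan ignores the index baseline. It does not: the Follow-up section uses it in a before-after comparison. Nor is the index comparison biased. With 1:1:1 randomization, a follow-up-only contrast is unbiased apart from attrition, and an unadjusted test is a legitimate choice. Chi-square also suits the outcome, since having multiple partners is already a category in the stated definition; modelling the partner count would replace the outcome. Regression to the mean is not a strong charge either, because eligibility asks only for sex with a man at any time, not for recent high risk. All of this stands, and it reduces the index point to precision on a secondary outcome. What it leaves is that the protocol has fixed the test and its data source. This is therefore a stated choice that can be improved, not a detail left to an analysis plan.

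A reader might also infer that the plan claims an effect of the arms on alters' behaviour. The text speaks only of comparing arms. Describing who each arm reached is in keeping with the trial's aims, and the third secondary outcome already lists alters' past experiences and sexual behaviour. The question about sex after self-testing sits among the experience and perception items, not in the definition of risk behaviour. It also cannot be shown that alters' answers wholly precede contact with the kit, or that the post-test item must be near zero, because the intervals from receipt to test and from test to upload are not given. These limits are accepted. They do not remove the mismatch between an item about behaviour after testing and a survey completed at upload, nor the need to say how an arm difference in alters should be read.

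**Conclusion.** The point holds in two limited parts.

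**Indexes:** the planned arm comparison is valid but less precise than the collected data allow. The gain depends on a baseline-to-follow-up correlation that the protocol does not give. On the assumptions above, power moves from 0.48 to between 0.52 and 0.60 for yes/no items correlated at 0.3 to 0.5; the 0.77 at r = 0.7 is optimistic for binary items. The before-after comparison describes change and does not attribute it.

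**Alters:** a between-arm difference in their reported risk behaviour would mainly reflect whom each arm reached. The rejection rates of 24% to 77% rest on assumed differences in composition and on independence of alters; they show that such a finding is possible, not that it is expected.

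The outcome is secondary, and nothing here touches the primary outcomes.

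**What to change.** **Indexes.** Keep the stated binary outcomes. Compare arms at 3 months by logistic regression with arm and the same item at baseline as covariates, for the same three pairs of arms. Confirm that the item and its recall window are the same in both surveys: the Follow-up section says risky sexual behaviour is asked at 3 months, but the account of that survey under Measures does not list it. Present before-after change by arm as description, and say so in the Follow-up section so that it agrees with the Secondary analysis section.

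**Alters.** State that between-arm differences in alters' risk behaviour describe the people each arm reached and are not an intervention effect on behaviour. Reconcile the item on sex after self-testing with a survey completed at upload, or leave it out of the between-arm tests.

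**Cost.** The change is to analysis and interpretation wording. It needs no new data as long as the index item is the same in both surveys, and the Trial status section says analysis has not begun. One alter outcome becomes descriptive. The logistic model gives an odds ratio conditional on baseline, so the simple percentages by arm should be reported beside it.
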